## Abstract

**Introduction:**

A healthy diet improves glycaemic control and reduces cardiovascular risk in type 2 diabetes (T2D). However, access to dietitians is limited. Several countries have implemented mandatory interpretive front-of-pack labelling to guide consumers towards healthier food choices, but Sweden has not. Smartphone applications may offer an alternative platform to provide such information. This study evaluates the dietary and clinical impact of a novel application providing interpretive labelling to Swedish adults with T2D.

**Methods and analysis:**

This is a fully decentralised randomised controlled trial. 900 individuals with T2D for ≥2 years who regularly shop for groceries will be recruited via general practices and community advertisements. Participants will be randomised to receive either: (1) access to the *FoodSwitch* mobile application plus standard written dietary advice, or (2) standard written dietary advice only. The *FoodSwitch* application allows users to scan barcodes on packaged foods to receive recommendations of healthier alternatives within the same category. The primary outcome is the difference in change in mean self-measured glycated haemoglobin between groups after 6 months. Secondary outcomes include differences in changes in waist circumference, body weight, quality of life, medication use, hospitalisations and all-cause mortality at 26 weeks. Exploratory outcomes include omics analyses. Recruitment is ongoing. Expected study completion on 31 December 2026.

**Ethics and dissemination:**

The trial has received ethical approval from the Swedish Ethical Review Authority (2023-06622-01, 2024-06668-02, 2024-07357-02 and 2025-01095-02) and is performed in line with World Medical Association Declaration of Helsinki and the General Data Protection Regulation. Results will be published in a peer-reviewed international journal.

**Trial registration number:**

NCT05977218.

STRENGTHS AND LIMITATIONS OF THIS STUDYThe study is fully decentralised, enabling national recruitment and participation without site visits.Use of digital consent, self-administered anthropometrics and dried blood spot sampling minimises participant burden and costs.The intervention is based on an evidence-informed, widely available mobile platform (*FoodSwitch*) adapted to the Swedish food market.Limitations include self-reported dietary and anthropometric data, potential selection bias towards digitally literate participants and inability to blind participants to allocation.

## Introduction

### Background and rationale

Diabetes, a major risk factor for cardiovascular disease, affects approximately 6.2% of the Sweden population, with 88% of cases managed in primary care.^1 2^ Obesity and lifestyle factors are key drivers in the development of type 2 diabetes (T2D), and with over half of adults in Sweden overweight or obese, the prevalence continues to rise.^3 4^ Two out of five persons with T2D in Sweden are overweight, and another two out of five are obese.^2^ Dietary change is a first-line recommendation in clinical guidelines as it can reduce body weight, improve glycaemic control and lead to T2D remission.^3^ However, many individuals struggle to follow dietary advice.^5^

The WHO recommends mandatory front-of-pack nutrition labelling (FOPL) as a key public health strategy to promote healthier diets and reduce the burden of non-communicable diseases, which are the leading causes of death globally.^6^ Yet in Sweden, no mandatory FOPL system has been implemented. Furthermore, access to dietitians is limited.^7 8^ The voluntary Keyhole label is displayed exclusively on the healthiest products in each food category, thereby limiting its potential to influence consumer choices across the broader product spectrum. Selecting healthy products can be challenging due to the wide range of available products, and real-world interventions suggest that interpretive labelling improves dietary choices.^9^

Smartphone-based interventions for health behaviour change and disease management offer key advantages, including low cost and broad scalability,^10 11^ and 99% of Swedes own a mobile phone.^12^ Studies using smartphone applications, text messaging or telehealth video conferencing to support healthy eating have shown promising results for weight loss in overweight and obese adults.^13^ Numerous applications aimed at promoting healthy eating, cooking and weight control are available, but the majority have not been evaluated for their effectiveness.^14^ While mobile health (mHealth) tools have been shown to improve diet and clinical management in patients with T2D,^15^ no evidence-based such tools for dietary advice are currently available in Sweden. Sweden’s high digitalisation (99% smartphone ownership) and lack of mandatory FOPL make it an ideal setting for testing scalable digital dietary interventions.

### Objectives

The aim of the current study is to evaluate the effect of a novel smartphone app (*FoodSwitch),* in addition to standard written dietary advice, compared with standard written dietary advice alone, on blood glucose control (glycated haemoglobin, HbA1c) in individuals with T2D.

## Methods and analysis

### Study design and timeline

This will be a trial of 900 participants randomised to *FoodSwitch* or control (1:1 allocation) with a 26-week follow-up (table 1). The study will be fully decentralised, with recruitment, inclusion and data collection all performed remotely. Recruitment started on 25 August 2025 and is estimated to continue until 31 December 2026. Study completion is estimated to be 31 December 2031.

**Table 1 T1:** Schedule of enrolment, interventions and assessments

	Screening	Run-in period 1	Run-in period 2	Postallocation period				Long-term follow-up
	0–4 weeks prior	0–3 weeks prior	0–6 weeks prior	0	6 weeks	13 weeks	26 weeks	3–7 years
Enrolment								
Digital consent	X							
Screening questionnaire	X							
Randomisation				X				
Intervention and control								
The *FoodSwitch* app								
Standard written dietary advice								
Assessments								
Questionnaires		X			X	X	X	
Collection of receipts		X				X	X	
Anthropometric measurements			X			X	X	
Blood samples			X			X*	X	
National register data							X	X

*Week 13, only glycated haemoglobin.

### Inclusion and exclusion criteria

Inclusion criteria will be age between 18 and 75 years, self-reported T2D with a duration of ≥2 years and does grocery shopping at physical grocery stores. Exclusion criteria will be no access to *BankID* (a secure electronic identification system, widely used in Sweden) or failure to complete eligibility screening and run-in periods 1 (questionnaires and grocery receipt collection) and 2 (self-measurement of waist circumference, body weight and self-collection of capillary blood samples).

### Recruitment

Participants will be recruited by clinicians in primary care, as well as through social media, patient associations, letters and newspaper advertisements. Individuals from all parts of Sweden will be invited to participate.

Individuals interested in participating will be directed to *minforskning.se* (MinForskning AB, Uppsala, Sweden), an online platform for digital consent.^16^ The platform will present detailed written information about the study, including the study’s purpose, risks and benefits and participants’ right to withdraw at any time, and allow individuals to provide digital consent (online supplemental material). The platform uses *BankID* (Finansiell ID-Teknik BID AB, Stockholm, Sweden), a secure digital identification system accessible to 99.3% of Swedish adults 75 years or younger (Personal Communication with BankID Customer Support, 12 August 2025). No study-specific procedures will be performed before consent has been provided. *Minforskning.se* will securely store the signed consent forms and provide participants with copies on request. Participants can withdraw their consent to participate at any time, with no influence on further clinical care or treatment. Data collected before any withdrawal are retained and included in analyses.

10.1136/bmjopen-2025-110141.supp1Supplementary data

10.1136/bmjopen-2025-110141.supp2Supplementary data

After providing consent, participants will be asked to complete a questionnaire to confirm eligibility. Those who respond within 28 days may proceed to run-in period 1.

### Screening eligibility and run-in periods

In run-in period 1, participants will complete questionnaires on demographics, household characteristics, grocery purchasing habits, medical history and medications and upload grocery shopping receipts from 1 week of typical grocery purchases. Reminders to complete the questionnaires and upload receipts will be sent after 7 and 14 days. Participants who complete these tasks within 21 days may proceed to run-in period 2.

In run-in period 2, participants will be asked to measure their waist circumference and body weight and to self-collect capillary blood on filter papers (see the Assessments section). Participants who complete the capillary blood test within 42 days will proceed to randomisation.

### Randomisation

Participants will be randomised to the intervention or control in a 1:1 ratio using REDCap (Vanderbilt University, Nashville, Tennessee, USA) based on a computer-generated randomisation list. Healthcare providers, study investigators and data analysts will be blinded, while participants will not be blinded.

### Intervention

Participants randomised to the intervention group will receive access to the *FoodSwitch* app with the *DiabetesSwitch* filter for 26 weeks, in addition to standard dietary advice (see the Control section). The *FoodSwitch* platform, developed by The George Institute for Global Health (Sydney, Australia), includes a database of over 700 000 products across 12 countries. When grocery shopping, the app is used to scan barcodes on packaged food items, providing interpretive nutritional information using a traffic light colour-coded ranking based on energy, fat, sugars and salt content and suggesting alternative products, within the same product category, with better nutritional quality (figure 1). For this trial, data from the Dabas open database^17^ (Bayn Solutions AB, Stockholm, Sweden) and the three largest grocery store retailers in Sweden, representing 70.9% of the market and collected through website scraping, were processed to incorporate the nutrient profiles of approximately 57 000 Swedish food products into the platform database.^18^ Food products were then manually categorised at the product level to enable the identification of healthier alternatives within the same category. In cases where categorisation was unclear, two research assistants independently assessed the product to determine the most appropriate classification.

**Figure 1 F1:**
[figure not shown]
Two screenshots from the *DiabetesSwitch* mobile application. The app evaluates a selected food product (top section) based on five nutritional components: energy, protein, saturated fat, net carbohydrates, fibre and salt, using a traffic-light colour-coded rating system (green=better, yellow=intermediate, red=worse and grey=not available or not rated). Below the selected product, the app suggests alternative options with more favourable nutritional profiles, using the same visual scale to allow for direct comparison across all components.

The *DiabetesSwitch* filter, also developed by The George Institute for Global Health, is adapted for individuals with T2D and integrated into the *FoodSwitch* app. *DiabetesSwitch* tailors nutrient displays and recommendations for individuals with T2D. While *FoodSwitch* displays energy, saturated fat and salt, *DiabetesSwitch* also includes proteins, net carbohydrates and fibre, disqualifying products with low fibre content, thereby supporting better glycaemic control. The app functions by scanning a product’s barcode, identifying its nutrient profile from a database of manufacturer-provided on-pack data, and ranking similar products based on the sum of total energy and energy from net carbohydrates, with lower totals ranked as healthier.

#### Control

Participants randomised to the control group will receive standard written dietary advice in the form of a pamphlet widely used in Swedish primary care, sent via postal mail.^19^

### Endpoints

#### Primary endpoint

Difference in change in mean HbA1c between intervention and control at 26 weeks will be examined using linear regression. Models will be adjusted for baseline characteristics, including age, sex and baseline values, to increase power, as advised by regulatory authorities.^20^

#### Secondary endpoints

Difference in change in national registry-based data on medication use, hospitalisations, outpatient visits and diabetes complications, self-measured waist circumference and body weight, self-reported quality of life and dietary self-efficacy, between intervention and control at 26 weeks, will be examined using linear regression. Difference in all-cause mortality between intervention and control at 26 weeks will be analysed using Cox proportional hazards models. Registry-based outcomes will also be assessed and compared between intervention and control at 2 and 5 years, respectively. Additionally, changes in patterns of food purchasing, identified from receipts and focusing on fibre-rich foods (such as legumes, vegetables, fruits, nuts and whole grains), processed foods, dairy products (low- and full-fat) and confectionery, between intervention and control at 13 and 26 weeks, will be examined using linear regression.

#### Exploratory endpoints

The omics data include proteomics and metabolomics, which may reveal biological mechanisms underlying the dietary intervention. These data will be analysed using advanced, multivariate data analysis,^21^ which has the potential to identify a pool of biomarkers with superior diagnostic and prognostic performances compared with a single-marker approach. These exploratory analyses will be specified after the conclusion of the study and may include partial least squares regression analyses, cluster analysis and principal component analysis. Before such analysis, principal component analysis will be used to check for multivariate outliers. The guidelines for interpreting and presenting results presented by Wheelock and Wheelock will be followed.^21^ Moreover, network construction to organise and make sense of the large amount of omics data will be performed using bioinformatics in order to find functions, pathways or networks involved in the biological mechanisms affected by the intervention.

### Assessments

Data collection will be performed in a decentralised manner, through the use of digital tools and blood samples sent by post, coordinated at Linköping University, Sweden. All participants will be asked to provide the following information.

#### Questionnaires

Participants will be asked to fill in questionnaires via *Symptoms* (Symptoms Europe AB, Uppsala, Sweden), a validated health data collection online platform accessible via smartphones, tablets and computers.^22^ Patient-reported outcome measures have been used sparingly in clinical practice, but digital versions are as effective, or more effective than paper forms.^23 24^ Advantages include simplified data management, improved completion rates through digital reminders and novel data types, such as three-dimensional pain drawings.^24–26^

Questionnaires cover quality of life (EQ-5D-5L), digital tool usage, grocery shopping practices and self-efficacy, sleep patterns, physical activity, dietary habits, alcohol and tobacco use, as well as open-ended symptom reporting and participant-generated symptom drawings. These questionnaires will be collected during run-in period 1 and at 13 and 26 weeks during the postallocation period, and EQ-5D-5L will also be collected at 6 weeks during the postallocation period. During run-in period 1, a medical history questionnaire will also be collected. Some questionnaires will also be available for spontaneous completion at any time as chosen by the participant.

#### Anthropometrics

Via postal mail, participants will receive a tape measure with written instructions for self-measurement of waist circumference. Those with access to a home scale will also receive instructions for measuring body weight. For participants with missing self-reported weights, data from the Swedish National Diabetes Register will be used. Measurements will be collected during run-in period 2 and at 13 and 26 weeks during the postallocation period.

#### Blood samples

Participants will receive a blood sample collection kit from Vitas Analytical Services AS (Oslo, Norway) containing an alcohol swab, two lancets, two filter papers (each with four collection spots) and a return envelope. The kit will be sent during run-in period 2 and at 13 and 26 weeks during the postallocation period. After an 8-hour overnight fast, participants will be instructed to collect capillary blood droplets onto each designated filter paper spot via finger prick and return the dried samples by postal mail.

For the collection of the dried blood spots on filter papers, the participants will thoroughly wash and disinfect their hands with alcohol, followed by air drying. A lancet will then be used to puncture the third or fourth digit, and the initial drop of blood formed will be discarded. The finger will then be gently massaged to facilitate the formation of a sufficient blood droplet, which will be dropped onto the first circle of the filter paper, ensuring no contact with the surface of the filter paper. Subsequently, the finger will again be massaged to produce additional droplets, which will be used to fill the remaining circles of the filter papers. Following sample collection, the blood cards will be left to air dry at ambient room temperatures for 3 hours, after which they will be stored at −80°C until further analysis.

A novel collection of capillary blood onto filter paper using a lancet offers advantages to venepuncture, including minimal invasiveness, low cost, no need for healthcare personnel and simplified transport via regular mail.^27 28^ Dried blood spots on filter paper have been used in several large-scale studies, and HbA1c can be reliably estimated.^28–33^ In the 12-week DIATEST-HELP (DIgitAl diabeTES Treatment – the Healthy Eating, heaLthy Patients) pilot study, almost 90% of participants were comfortable with performing the self-administered blood test.^34^

### Register data

Several national Swedish registers will be used for long-term follow-up of cardiovascular outcomes and diabetes complications, as well as detailed baseline characteristics. The Swedish National Patient Register will be used to collect data on hospitalisations and hospital outpatient visits, including patient demographics, caregiver information, date of admission/discharge or visit, diagnosis (primary and secondary) and clinical procedures; The Swedish Cause of Death Register will be used to collect data on dates and underlying causes for all deaths; The Swedish Prescribed Drug Register will be used for information on all dispensed drug units including drug identification number, number of dispensed units, costs, patient demographics (including age and sex), date of prescription and dispensation and code for caregiver; The Swedish National Diabetes Register will be used for data on individuals with diabetes, including treatment, risk factors (eg, blood lipids, physical activity, office blood pressure) and relevant complications (eg, diabetic foot ulcers, retinopathy, kidney function).

### Sample size

A total of 714 participants (357 in each arm) will provide 80% power (two-sided, α=0.05) to detect a 3 mmol/mol difference in change in HbA1c between intervention and control groups, assuming an SD of 14 mmol/mol.^35^ A 3 mmol/mol difference was selected as a clinically meaningful effect, comparable to that achieved with commonly prescribed glucose-lowering medications such as thiazolidinediones, biguanides and sodium-glucose cotransport-2 inhibitors.^36^ To allow for up to 20% drop-out, 900 participants (450 per arm) will be recruited.

### Data management

During the study, data will be collected in the respective systems. Sent and received test kits, as well as data from *Symptoms*, will be recorded in REDCap. After the completion of the study, these data will be merged into a single database. If applicable, missing data will be addressed using listwise deletion or imputation, depending on the degree and pattern of missingness.

Participant inclusion and data collection will be overseen by the study investigators as needed, independently of the sponsor and funders. A formal data monitoring committee will not be established, as the study does not involve the evaluation of a pharmaceutical intervention.

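### The missing-data rule leaves listwise deletion open for the primary HbA1c analysis, with no criterion for choosing it and no stated role for the week-13 HbA1c; bias follows if loss tracks HbA1c differently by arm

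*Protocol article*

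**What the plan says.** All references are to the protocol article.

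- **Data management**: "missing data will be addressed using listwise deletion or imputation, depending on the degree and pattern of missingness". This is one general sentence for the whole trial. It gives no threshold, no imputation model and no order of primary and sensitivity analyses.
- **Primary endpoint**: "Difference in change in mean HbA1c between intervention and control at 26 weeks will be examined using linear regression". On covariates: "Models will be adjusted for baseline characteristics, including age, sex and baseline values". No post-baseline HbA1c is named.
- **Study design and timeline**, footnote to Table 1: "Week 13, only glycated haemoglobin". **Blood samples** (under Assessments) agrees: "The kit will be sent during run-in period 2 and at 13 and 26 weeks during the postallocation period". HbA1c is therefore requested from everyone at week 13, and no endpoint or model in the article uses it.
- **Recruitment**: "Data collected before any withdrawal are retained and included in analyses".
- **Sample size**: "To allow for up to 20% drop-out, 900 participants (450 per arm) will be recruited".
- **Randomisation**: "Healthcare providers, study investigators and data analysts will be blinded, while participants will not be blinded".

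**The concern.** Listwise deletion and imputation rest on different assumptions and can give different primary estimates. The article does more than stay silent here. It states a rule, and the rule defers the choice until the missingness is known without saying what degree or pattern leads to which method.

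Listwise deletion of the 26-week regression is unbiased if, given arm, age, sex and baseline HbA1c, being observed at week 26 is unrelated to the outcome. Participants know their allocation, follow-up is entirely remote and up to a fifth may be lost, so this cannot be taken for granted. If app users who are doing badly leave more readily than comparable controls, those who remain make the app look better than it is.

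There is also an internal tension. A participant with a week-13 value who then withdraws has given post-randomisation HbA1c data. Listwise deletion removes that participant from the primary model, although the Recruitment section says such data enter the analyses. The two statements need reconciling.

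**Working it through.** **1. The plan's own figures.** Inputs from the Sample size section: difference 3, SD 14, two-sided α 0.05, 357 per arm.

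- SE = 14 × √(2/357) = 1.048; 3/1.048 = 2.863; power = Φ(2.863 − 1.96) = 81.7%. The stated 80% is met. The formula itself needs 342 per arm, so 714 is slightly conservative.
- 714/0.8 = 892.5, rounded up to 900. At 20% loss, 360 per arm remain: SE = 14 × √(2/360) = 1.044 and power 82.0%.

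Listwise deletion at the planned loss is therefore not a power problem. The question is bias.

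**2. What was compared.** Simulated trials with 450 per arm, analysed in two ways:

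- *Listwise*: 26-week HbA1c regressed on arm and baseline in those observed at week 26. With baseline in the model, analysing the change gives the same arm coefficient.
- *Using week 13*: regress week 13 on arm and baseline (arm coefficient a), then week 26 on arm, baseline and week 13 (coefficients b for arm, c for week 13). The effect is b + c × a.

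Negative bias favours the app.

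**3. Equal 20% loss in both arms.** Assumed: SD 14 at each visit; correlations baseline–13, baseline–26 and 13–26 of 0.7, 0.6 and 0.8; 40% of the loss random and before week 13; the rest after week 13, with the stated log-odds per SD of worse week-13 change. There is no true effect, and 1,500 to 2,000 trials were run per scenario.

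| Dependence, app / control | Listwise bias | Type I error |
|---|---|---|
| none / none | 0 | about 5% |
| 1 / 1 | −0.01 | 5.6% |
| 0.25 / 0 | −0.20 | 6% |
| 0.5 / 0 | −0.42 to −0.44 | 6.7% to 9.5% between runs |
| 1 / 0.5 | −0.38 | 7% |
| 1 / 0 | −0.79 to −0.80 | 16% to 17% |
| opposite directions | −1.63 | 51% |

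Check on the 1 / 0 row: with an SE of 0.834, 0.79/0.834 = 0.947, and Φ(−1.96 + 0.947) + Φ(−1.96 − 0.947) = 15.7%. The estimator using week 13 had bias of about 0.01 in this row. With a true effect of 3, listwise deletion gave about 3.8 and the week-13 estimator about 3.0.

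Scale: with SD 14 at each visit, the SD of change is 14 × √(2 × (1 − 0.6)) = 12.5. Reading the plan's 14 as the SD of change multiplies the biases by 14/12.5 = 1.12 (−0.79 becomes −0.88). Type I error is unchanged because the SE scales too.

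**4. Unequal loss, 20% overall.** Assumed: SD of change 14; correlations baseline–13, baseline–26 and 13–26 of 0.6, 0.5 and 0.7; all week-13 values observed; 2,000 trials. Loss is app / control.

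| Loss depends on | Loss | Listwise bias (type I error) | Bias using week 13 |
|---|---|---|---|
| nothing, or baseline only | 25% / 15% | about 0 (4% to 6%) | about 0 |
| week-13 change, same in both arms | 25% / 15% | −0.48 (7.9%) | 0 |
| week-13 change, app only, log-odds 0.5 to 1 | 25% / 15% | −0.65 to −1.24 (10% to 29%) | about 0 |
| week-13 change, app only, log-odds 1 | 30% / 10% | −1.47 (36%) | about 0 |
| unseen week-26 value | 25% / 15% | −0.85 to −2.28 | −0.60 to −1.60 |
| unseen week-26 value, app only | 30% / 10% | −2.73 | −1.93 |

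Over other assumed correlations, the 25% / 15% app-only case with log-odds 1 ranges from −0.86 to −1.55.

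**5. Reading.** Unequal rates alone do no harm, and neither does the same dependence at equal rates. Bias needs dependence on HbA1c beyond the model's covariates, together with a difference between arms in that dependence or in the rate. Week 13 removes the bias when loss depends on what was seen at week 13. It removes only part when loss depends on the unseen final value.

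**The case against.** - **The mechanism may be weak.** The section on laboratory analysis of blood samples says participants get their HbA1c results only when the trial ends, so they do not routinely know their week-13 value. The exception for results showing deterioration (Safety considerations) is not arm-specific. This stands, and it makes log-odds of 1 in one arm only a strong assumption. It does not remove indirect routes: participants measure their own weight and waist at week 13.
- **Imputation could use week 13.** A reader might infer that the plan discards the week-13 HbA1c. The text does not say so. Imputation is one of the two named options, and its model may be set out in a full protocol or analysis plan that is not shown. What stands is that the regression as described and listwise deletion make no use of it.
- **The later choice need not be driven by the result.** A reader might infer that the method will be picked with the treatment effect in view. The stated basis is missingness, and analysts are to be blinded, so the documents do not support that reading. The undefined criterion remains.
- **The planned regression is standard.** A baseline-adjusted analysis at the final visit is valid, and without dependent loss the week-13 model reduces the SE by only about 2% to 4%. Requiring both run-ins before randomisation also screens out some likely non-completers. All this is true, but it defends the regression and not the open missing-data rule.

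**Conclusion.** The point holds in a conditional form. The article leaves listwise deletion available for the primary comparison on an undefined criterion, gives week-13 HbA1c no stated role there, and is in tension with its own statement on data obtained before withdrawal.

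How far this could move the result depends on correlations, loss by arm and loss mechanisms that the documents do not give. When loss depends on observed week-13 HbA1c, the assumed cases run from no bias, through about 7% to 26% of the 3 mmol/mol target (0.2/3 to 0.79/3) for app-only dependence at equal 20% loss, to about half of it (1.63/3 = 54%) in extreme cases.

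A reader might go further and conclude that the app effect will be inflated, or that differential drop-out by itself biases it. Neither follows from the documents or the calculation. This should be fixed, but it does not invalidate the design.

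**What to change.** Before the data are merged, name one primary method that uses week-13 HbA1c. Either of these would serve:

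- a mixed model for repeated measures on HbA1c at weeks 13 and 26 in all randomised participants, with arm × visit, baseline HbA1c × visit, age, sex and an unstructured covariance; the 26-week arm contrast is the primary estimate; or
- multiple imputation by arm, with week-13 HbA1c in the imputation model, followed by the regression already planned.

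Make listwise deletion a sensitivity analysis. Add a delta-adjusted analysis for data missing not at random, because week 13 only partly corrects loss that follows the unseen 26-week value. Reword the Data management sentence so that it agrees with the Recruitment section on data obtained before withdrawal.

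The cost is a few sentences and slightly more analysis work. No extra samples or participants are needed, and nothing is lost if drop-out proves unrelated to HbA1c.
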